#### Sample size calculation

2.2.4

An *a priori* power analysis was conducted to calculate the minimum sample size required for this study, following established statistical procedures (Perugini et al., 2018; Taccini et al., 2022). The G*Power software (V.3.1.9.2) (Faul et al., 2007, 2009) was utilized to determine the required sample size for repeated measures analysis of variance (ANOVA) with within-between interaction. The research protocol involves four assessment timepoints, with treatment condition as between-group variable (TAU vs. TAU + psychoeducation vs. TAU+R-TEP) and time as within-subject variable (T0, T1, T2, and T3; see dedicated section).

Given the absence of prior studies implementing this specific intervention protocol, conservative a priori parameters were adopted. These were informed by examining previous studies utilizing similar interventions (though not identical), comparable target samples, and similar constructs. The effect size *f* was set to 0.15 (small-to-medium effect size) and the correlation among repeated measures was set to 0.35. Type I error rate probability (*α*) was set to 0.05 (two-sided), and power (1-*β*) was set at 0.80 (Cohen, 1988; Eid et al., 2017; Perugini et al., 2018).

G*Power analysis indicated 80% probability of correctly rejecting the null hypothesis of no significant group-by-time interaction effect with an overall sample of 102 participants (approximately 34 subjects per group). Based on average patient flow to the unit, to account for an anticipated attrition rate of approximately 20%, the study aims to recruit at least 122 patients, ensuring adequate statistical power for the planned analyses.

The three groups will each comprise a minimum of 34 patients: (A) Control group (G1): Patients receiving standard routine psychological support (TAU); (B) Active control group (G2): Patients receiving weekly psychoeducation session plus TAU; (C) Experimental group (G3): Patients receiving EMDR R-TEP intervention plus TAU.

This sample size is highly feasible considering service patient flow while simultaneously permitting statistical analyses generating reliable estimates.

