#### Randomization and blinding

2.2.5

The study employs a single-blind RCT design. Participant allocation to one of the three groups (TAU vs. TAU + psychoeducation vs. TAU+R-TEP) will follow rigorous procedures ensuring allocation concealment.

First, each participant will be assigned a unique identification code ensuring individual anonymity. Second, group allocation will be conducted through dedicated web-based software (Randomization.com) (Randomization, 2025) by two independent persons meeting the following requirements: (1) external to the project; (2) unaware of study objectives; (3) with no access to participant information; and (4) without mutual contact. If any condition is not met, these individuals will be replaced. This procedure ensures proper allocation concealment. Regarding blinding, participants are blinded to group assignment rationale, while treating clinicians are necessarily aware of intervention type given the nature of psychological treatments. Participants will be assigned to conditions within seven working days from baseline assessment.

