#### Control group (G1): treatment as usual (TAU)

2.3.1

Patients in the control group will receive unstructured psychological support sessions (without pre-established protocol) aimed at: reviewing individual history before and after disease discovery; exploring emotional experiences related to illness; identifying and strengthening individual resources; reducing psychological risk factors; promoting illness acceptance; and enhancing adherence to medical prescriptions and treatments. This approach reflects standard clinical practice in psycho-oncology settings and serves as the reference condition against which structured interventions are compared. TAU does not involve specific psychoeducation protocols or EMDR. However, if ongoing clinical monitoring during the therapeutic course reveals that a patient assigned to TAU would benefit more from a structured intervention (i.e., psychoeducation or EMDR R-TEP), clinicians will prioritize patient wellbeing and provide the most appropriate treatment. In such cases, the participant would be excluded from statistical analyses to maintain methodological rigor – as treatment crossover would violate the original randomized group assignment and compromise between-group comparability.

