Regarding potential adverse events, psychoeducational interventions may occasionally elicit emotional activation or transient distress when addressing trauma-related content or body image issues. Clinicians will monitor for such reactions throughout the therapeutic course. Management of adverse events will be handled at clinical discretion – given that the heterogeneity of possible reactions precludes a standardized intervention protocol. All adverse events will be documented in the study database. Should a participant experience recurrent or severe adverse reactions compromising their clinical stability, or when clinically indicated, they will be reassigned to TAU and excluded from statistical analyses – as treatment crossover would violate the original randomized group assignment and compromise between-group comparability.

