Regarding potential adverse events, EMDR-based interventions may occasionally elicit transient distress, emotional activation, or temporary symptom exacerbation during trauma reprocessing (van der Hart et al., 2006). Trained clinicians will monitor for such reactions throughout the therapeutic course, including transient dissociative responses, heightened anxiety, or emotional dysregulation. Management of adverse events will be handled at clinical discretion, or – when available – in line with EMDR guidelines. All adverse events will be documented in the study database. Should a participant experience recurrent or severe adverse reactions compromising their clinical stability, or when clinically indicated, they will be reassigned to TAU and excluded from statistical analyses – as treatment crossover would violate the original randomized group assignment and compromise between-group comparability.

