### Statistical analysis

2.6

Statistical data analyses will be performed using R software (R Core Team, 2017). Throughout data collection duration, *in itinere* statistical analyses will verify data quality and potential bias absence. Regarding missing data management, participants who discontinue the study (dropouts) will be excluded from analyses due to concerns about response validity. Similarly, assessment batteries with more than 10% missing items will be considered invalid and excluded. For remaining missing data within valid batteries, appropriate handling methods (e.g., multiple imputation, full information maximum likelihood) could be employed depending on missing data patterns and mechanisms.

Preliminary analyses will verify group homogeneity regarding relevant variables (age, comorbidity, social support, etc.) and possible intervening variable influence (covariates). If deemed appropriate and/or if significant heterogeneity is detected between groups, such variables will be included as covariates in the analysis models. Preliminary analyses will also verify psychometric instruments’ internal consistency (McDonald’s omega) (McDonald, 1999).

Both group-level aggregate analyses and individual change-focused evaluations will be employed. At group level, longitudinal changes will be examined using appropriate linear models for repeated measures data (e.g., linear mixed models or repeated measures ANOVA, or Bayesian approaches), depending on data characteristics such as distribution, missing data patterns, and sphericity assumptions (Howell, 2013; Darlington and Hayes, 2017; van den Bergh et al., 2023). Also, if appropriate, multilevel analysis – random slopes and/or random intercepts – may be implemented in the models (Hox et al., 2017; Heck and Thomas, 2020; Finch and Bolin, 2024). Model selection will be guided by standard diagnostic procedures. All models will test the interaction between time and intervention group – and where appropriate – controlling for individual variability and potential covariates identified in preliminary analyses.

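### Patients who change treatment after randomisation are excluded from the analysis in all three arms, so the groups compared are no longer the randomised ones

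*Protocol article*

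**What the plan says.** The rule appears once under each arm of the protocol article.

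- **TAU (section 2.3.1).** If monitoring during the course "reveals that a patient assigned to TAU would benefit more from a structured intervention", she is given that intervention. Then: "In such cases, the participant would be excluded from statistical analyses to maintain methodological rigor".
- **Psychoeducation (2.3.2) and R-TEP (2.3.3).** The trigger is worded identically in both: "Should a participant experience recurrent or severe adverse reactions compromising their clinical stability, or when clinically indicated". The consequence is that "they will be reassigned to TAU and excluded from statistical analyses".

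All three sections give the same reason, namely that crossover would breach the randomised allocation and spoil comparability between groups.

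Three other statements bear on this. Under Randomization and blinding (2.2.5), "treating clinicians are necessarily aware of intervention type given the nature of psychological treatments". Under Statistical analysis (2.6), "participants who discontinue the study (dropouts) will be excluded from analyses due to concerns about response validity", and Timeline and assessments (2.4.2) also leaves out patients who withdraw. In 2.3.2 and 2.3.3, the sentence just before the reassignment rule reads "All adverse events will be documented in the study database".

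**The concern.** Randomisation makes the three groups comparable at the moment of assignment. They remain comparable in the analysis only if membership does not depend on what happens afterwards. Here it does, for four reasons:

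1. Removal follows from the clinical course under treatment.
2. The decision is made by clinicians who know the arm.
3. The trigger in TAU is expected greater benefit elsewhere; in the other two arms it is an adverse reaction or a clinical indication.
4. The clinical-indication limb carries no criterion, so it can be applied differently from patient to patient and from arm to arm.

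At stake is the comparison that the trial exists to make, R-TEP against TAU and against psychoeducation, on both primary outcomes (PDI-R and PTSQ). If TAU loses patients who are doing poorly, TAU looks better than it was. If R-TEP or psychoeducation loses patients who reacted badly, those arms look better than they were. No passage provides an analysis of all randomised patients, or a sensitivity analysis that keeps the switchers.

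**Working it through.** **1. The plan's own sample size.** Inputs from section 2.2.4: three groups, four timepoints, alpha 0.05, power 0.80; the effect size f "was set to 0.15 (small-to-medium effect size) and the correlation among repeated measures was set to 0.35". For the within-between interaction with sphericity assumed,

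λ = f² × N × m / (1 − ρ), df1 = (k − 1)(m − 1), df2 = (N − k)(m − 1).

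With N = 102, k = 3, m = 4: λ = 0.0225 × 102 × 4 / 0.65 = 14.12, df1 = 6, df2 = 297, power 0.807. The smallest N reaching 0.80 is 101 (power 0.802), and 102 is the next multiple of three. The stated 102 reproduces.

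**2. Shift in an arm mean.** The documents give neither a switching rate nor a correlation between removal and outcome, so both are assumptions here. Suppose the worst fraction q of an arm is removed on a state that correlates r with the outcome (higher score = worse). The mean of those left shifts by

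r × φ(z) / (1 − q), where z is the 1 − q quantile of the standard normal.

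- q = 10%: 0.1755 / 0.90 = 0.195 SD at r = 1, and 0.35 × 0.195 = 0.068 SD at r = 0.35.
- q = 15%: 0.2332 / 0.85 = 0.274 SD at r = 1, and 0.096 SD at r = 0.35.

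**3. Net effect on the R-TEP minus TAU difference when there is no true effect.** A negative value favours R-TEP.

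| Removed, R-TEP | Removed, TAU | r = 0.3 | r = 0.5 | r = 0.7 | r = 1 |
|---|---|---|---|---|---|
| 10% | 0% | −0.06 | −0.10 | −0.14 | −0.20 |
| 20% | 0% | −0.11 | −0.18 | −0.25 | −0.35 |
| 10% | 10% | 0 | 0 | 0 | 0 |
| 5% | 15% | +0.05 | +0.08 | +0.12 | +0.17 |

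**4. Type I error of a two-sided 5% pairwise test.**

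- Noncentral t, 34 per arm, df = 66, noncentrality = shift × √(34/2): 0.10 SD gives 0.41 and an error of 7%; 0.14 SD gives 0.58 and 9%; 0.274 SD gives 1.13 and 20%.
- Simulation, 40 per arm before removal, 6,000 runs: 10% against 0% gives 0.07 (r = 0.5) and 0.10 (r = 0.7); 20% against 0% gives 0.12 and 0.18; 10% against 10% gives 0.05.

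**5. Power at the plan's inputs.** All 122 recruited patients analysed: 0.883. With 20% removed in total (97 analysed): 0.783. If switchers are lost on top of 20% attrition: 0.756 with a further 5% (N = 92) and 0.727 with a further 10% (N = 87). The 0.883 assumes that the planned effect survives switching; dilution would lower it.

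**The case against.** The best defence is that the protocol's limitations section describes an initial efficacy trial, so the intended question may be how the treatments compare when taken as assigned. That is a legitimate question, but deleting switchers does not answer it with randomised groups. The set that remains has been selected by post-randomisation events. It can serve as a sensitivity analysis, not as the only analysis.

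A second objection carries more weight: the bias could be nil. If every arm loses the same share by the same mechanism, the shifts cancel (step 3). Nothing in the plan makes this likely, since the triggers differ, but nothing excludes it. The contrast between triggers should not be overdrawn either, because the clinical-indication limb in the two structured arms is open-ended and may work much like the TAU rule.

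Some stronger readings are tempting but not supported:

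- **Severe reactions vanish from the safety data, so R-TEP will look safer than it was.** Sections 2.3.2 and 2.3.3 say that all adverse events are documented in the database. What is excluded is the patient from the statistical analyses. Whether the safety tables include switchers is simply not stated.
- **Adverse events go unrecorded in TAU.** This would rest only on the absence of a sentence in a condensed article.
- **The worst responders are removed.** For TAU this is a reasonable inference, but the text speaks of likely greater benefit from another intervention.
- **The damage cannot be repaired by any model.** Exclusion from analysis is not erasure. T0 and T1 precede the intervention, and T2 and T3 can still be collected. The narrower statement holds: a model fitted only to the remaining patients does not restore the randomised comparison.

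**Conclusion.** The point holds for the analysis set. As written, the plan removes patients in every arm on the strength of post-randomisation judgements by clinicians who know the arm, and the dropout rules in 2.4.2 and 2.6 do not restore an all-randomised analysis. This is stated text, not detail left to an analysis plan.

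Size and direction cannot be determined from the documents. Under the assumptions shown, losing the worst 10% of one arm and none of its comparator moves the difference by about 0.07 to 0.20 SD (r from 0.35 to 1), with type I error of roughly 7 to 10% at r of 0.5 to 0.7. The figures of 0.27 SD and 20% are an extreme one-sided case: 15% removed, removal tracking the outcome perfectly, and none removed from the comparator. A reader might infer that the rule favours R-TEP. It does so only if R-TEP loses more, or more outcome-related, patients than TAU; heavier loss from TAU reverses the sign.

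It should be fixed before outcome data accrue, because T2 and T3 assessments not collected after a switch cannot be recovered later.

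**What to change.** - In 2.3.1, 2.3.2 and 2.3.3, strike only the exclusion clauses and their justification. In 2.3.2 and 2.3.3 the exclusion shares a sentence with the clinical reassignment rule, so the whole sentence must not be deleted. The clinical switching and reassignment wording stays untouched.
- In 2.6, state that the primary analysis includes every randomised patient in her assigned arm, whatever treatment she then received (treatment-policy strategy).
- State that T2 and T3 are collected after a switch as for everyone else.
- Align the dropout exclusions in 2.4.2 and 2.6 with this; otherwise editing the three arm sections does not deliver an all-randomised analysis.
- Report the number of switches and their reasons by randomised arm. Keep the analysis without switchers only as a labelled sensitivity analysis.
- State that adverse-event tables include switchers, by randomised arm.

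Cost: a protocol amendment in wording, some follow-up work for switchers, who remain in care, and some dilution of the estimated effect by switching. In return, patients now discarded contribute to the comparison.

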#### Active control group (G2): TAU plus psychoeducational intervention

2.3.2

Patients in the active control group will participate in two individual sessions weekly combining psychological support with psychoeducational protocol. The primary objective of psychoeducation sessions is providing information regarding psychological aspects and experiences of oncological illness, with specific focus on post-traumatic aspects related to diagnosis, subsequent surgical intervention, and body image modification. The secondary objective involves helping patients recognize and structure functional emotion regulation strategies, including tools for improving observation and description abilities regarding their emotions in the present moment.

The psychoeducational intervention was developed in accordance with core components identified in the psycho-oncology literature (Al-Alawi et al., 2022; Setyowibowo et al., 2022), including information provision, emotional expression, coping skills training, and social support (Ratti et al., 2017; Panzeri et al., 2022; Taccini et al., 2022, 2025).

The 8-week individual intervention is structured as follows: (1) psychoeducation on cancer diagnosis and psychological reactions; (2) psychoeducation on trauma and post-traumatic responses; (3) emotional recognition and validation; (4) emotion regulation strategies I (grounding, breathing, relaxation techniques); (5) emotion regulation strategies II (cognitive reframing of illness-related thoughts); (6) body image and femininity after surgery; (7) personal resources and social support; (8) integration and future planning. Each session lasts 60–90 min and follows a semi-structured format allowing clinical flexibility while maintaining content consistency across participants. A description of the intervention structure is provided in Supplementary Table S1.

Regarding potential adverse events, psychoeducational interventions may occasionally elicit emotional activation or transient distress when addressing trauma-related content or body image issues. Clinicians will monitor for such reactions throughout the therapeutic course. Management of adverse events will be handled at clinical discretion – given that the heterogeneity of possible reactions precludes a standardized intervention protocol. All adverse events will be documented in the study database. Should a participant experience recurrent or severe adverse reactions compromising their clinical stability, or when clinically indicated, they will be reassigned to TAU and excluded from statistical analyses – as treatment crossover would violate the original randomized group assignment and compromise between-group comparability.

#### Experimental group (G3): TAU plus EMDR R-TEP

2.3.3

Patients in the experimental group will participate in two individual weekly sessions receiving psychological support plus EMDR R-TEP protocol administration. While sharing the supportive elements of TAU, this condition adds the specific trauma-focused R-TEP protocol, allowing evaluation of the incremental benefits of EMDR-based intervention compared to both unstructured support (G1) and structured psychoeducation (G2). According to guidelines, the EMDR R-TEP intervention is structured in eight phases (Shapiro and Laub, 2008):

*History taking and case conceptualization*: Special attention to recent cancer diagnosis, traumatic experiences during medical investigations and diagnostic procedures, emotion-focused coping modalities and self-regulation capacity, vulnerability to traumatic experiences, triggers eliciting disease-related episodes, significant relational factors, and internal/external resource analysis.*Patient preparation* for subsequent protocol phases, with specific attention to patient safety and containment.*Assessment and target selection*: Targets relate to present dimension or recent past (i.e., cancer diagnosis). This phase utilizes subjective distress evaluation measured with Subjective Units of Distress (SUD) scale, ranging 0–10, where 0 represents distress absence and 10 represents highest distress level experienced.*Desensitization and reprocessing* through bilateral stimulation.*Installation* of positive cognition using bilateral stimulation sets.*Body scan*.*Closure*: If SUD remains > 2, an additional session will be considered.*Reevaluation*: Each session begins with patient distress reevaluation following prior EMDR session.

Treatment fidelity for the EMDR R-TEP intervention will be ensured through the following procedures: (a) all therapists delivering the R-TEP protocol are trained and certified EMDR practitioners; (b) therapists will follow the manualized eight-phase R-TEP protocol as described by Shapiro and Laub (2008); (c) regular clinical supervision will be provided throughout the study duration to monitor protocol adherence and address implementation challenges. Formal independent fidelity assessment (e.g., session recording and external rating) was not included due to resource constraints, representing a limitation that should be addressed in future replication studies.

Regarding potential adverse events, EMDR-based interventions may occasionally elicit transient distress, emotional activation, or temporary symptom exacerbation during trauma reprocessing (van der Hart et al., 2006). Trained clinicians will monitor for such reactions throughout the therapeutic course, including transient dissociative responses, heightened anxiety, or emotional dysregulation. Management of adverse events will be handled at clinical discretion, or – when available – in line with EMDR guidelines. All adverse events will be documented in the study database. Should a participant experience recurrent or severe adverse reactions compromising their clinical stability, or when clinically indicated, they will be reassigned to TAU and excluded from statistical analyses – as treatment crossover would violate the original randomized group assignment and compromise between-group comparability.

### Procedure

2.4

#### Enrollment and informed consent

2.4.1

Following Breast Unit referral, patients will undergo individual interviews with healthcare professionals (clinical psychologists/psychotherapists) who assess study eligibility based on inclusion/exclusion criteria. Eligible individuals will receive detailed study information to obtain informed consent. Participants will be informed that: (i) participation is voluntary; (ii) refusal or withdrawal has no repercussions on care access or quality; (iii) withdrawal is permitted anytime with data deletion option; (iv) no economic compensation is provided; (v) group assignment does not influence psychological support quality.

Consenting participants will proceed to subsequent research phases (assessment). All procedures conform to the Diagnostic-Therapeutic Care Pathway (PDTA) in effect within the Service (PDTA ASST-Rhodense n.6 Rev. 04 approved 27.01.2025).

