#### Timeline and assessments

2.4.2

According to the flowchart of the study (Figure 1), participants will undergo six different steps.

*Baseline T0* (post-diagnosis, pre-hospitalization, pre-surgery): Participants will complete clinical interview and self-report psychological assessment battery.*Surgery:* participants will undergo breast surgery.*Follow-up T1* (within 1 week post-surgery): Participants will complete clinical interview and repeat self-report instruments to evaluate temporal changes.*Group assignment:* Following T1 assessment, participants will be randomly assigned to one of three groups, then follow their respective 8-week psychological intervention.*Follow-up T2* (psychological intervention completion, within 3 months post-surgery): All participants will complete the psychological assessment battery again to evaluate temporal changes.*Follow-up T3* (within 3 months post-psychological intervention): All participants will complete the psychological assessment battery again.

Participants who withdraw (dropout) from the study will not have their data considered in analyses. However, these individuals will continue receiving treatment benefits from their assigned condition. To ensure complete and optimal data analysis, questionnaires presenting missing data will be excluded from the study (Pozzar et al., 2020) – though participants will continue benefiting from assigned treatment.

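### The withdrawal, data-deletion and exclusion rules are not reconciled with the rule that every adverse event is documented, so some harms could go uncounted and some could be lost for good

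*Protocol article*

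**What the plan says.** Four sets of rules in the protocol article bear on this.

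- **Recording.** For the R-TEP arm, section 2.3.3 states "All adverse events will be documented in the study database". Section 2.3.2 has the same sentence for psychoeducation. Neither makes an exception for withdrawal or deletion.
- **Withdrawal and deletion.** Section 2.4.1 lists what participants are told, including "refusal or withdrawal has no repercussions on care access or quality" and "withdrawal is permitted anytime with data deletion option". It does not say what deletion covers.
- **After withdrawal.** Section 2.4.2 states "Participants who withdraw (dropout) from the study will not have their data considered in analyses" and adds that "these individuals will continue receiving treatment benefits from their assigned condition". Section 2.6 repeats the exclusion: "participants who discontinue the study (dropouts) will be excluded from analyses due to concerns about response validity".
- **After a bad reaction.** Sections 2.3.2 and 2.3.3 provide that patients with repeated or severe reactions, or where clinically indicated, leave their arm: "they will be reassigned to TAU and excluded from statistical analyses".

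**The concern.** Each rule is ordinary alone. Together they leave adverse events unprotected in the patients most likely to have had one. Section 2.3.3 itself expects R-TEP to cause passing distress, temporary worsening of symptoms, dissociative responses and heightened anxiety in some patients. Any of these is a plausible reason to withdraw, or to be moved to TAU. Both groups then leave the analyses, and those who withdraw may also ask for deletion.

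What is at stake is the comparison of harm between arms. If events are counted only in patients who stay, an arm whose treatment drives people out can look safer than it is. Deletion differs from exclusion in one respect: an exclusion can be reversed later by analysing everyone randomised, but a deleted record cannot be restored. That part therefore has to be settled before patients consent.

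**Working it through.** The article gives no figure for this point, so the main check is textual: follow each type of patient through the rules.

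| Patient in R-TEP or psychoeducation | Event recorded when it occurs? | Record protected from deletion? | In the analyses? | Treatment afterwards |
|---|---|---|---|---|
| Has a reaction, stays in the study | Yes (2.3.2, 2.3.3) | Question does not arise | Yes | Assigned condition |
| Repeated or severe reaction, reassigned | Yes (2.3.2, 2.3.3) | Deletion not mentioned on this route | No (2.3.2, 2.3.3) | TAU |
| Has a reaction, withdraws, no deletion request | Yes | Not applicable | No (2.4.2, 2.6) | Assigned condition (2.4.2) |
| Has a reaction, withdraws, requests deletion | Yes, at the time | Not stated (2.4.1) | No (2.4.2, 2.6) | Assigned condition (2.4.2) |
| Withdraws, has an event later in continued therapy | Not stated for this case | Not stated | No (2.4.2, 2.6) | Assigned condition (2.4.2) |

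Three things follow.

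1. In every row but the first, the text takes the patient out of the analyses and makes no exception for safety data. This needs no deletion request.
2. Only patients who request deletion can lose the record itself, and only if deletion reaches adverse-event records. The text says neither that it does nor that it does not.
3. For a patient who withdraws because of a reaction, two rules meet. Section 2.4.2 keeps her on the assigned condition, whereas 2.3.2 and 2.3.3 can move her to TAU. The article does not say which applies.

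**How many patients?** The only related input is in section 2.2.4: "to account for an anticipated attrition rate of approximately 20%, the study aims to recruit at least 122 patients".

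- Attrition at the stated rate: 0.20 × 122 = 24.4, about 24 patients. The margin actually built in is 122 − 102 = 20.
- Per arm, if attrition is even and all of it follows allocation: 24.4 / 3 = 8.1, about 8 of 122 / 3 ≈ 41.
- Both conditions are assumptions. On the timeline in 2.4.2, allocation follows T1, so patients lost between T0 and T1 have no arm and no exposure to study therapy.
- Deletion uptake is not given. The possible range for deletions through withdrawal is 0 to about 24 overall, or 0 to about 8 per arm.
- No number is given for patients reassigned after reactions, so none can be added.

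**What a few lost events could do (illustration only).** Suppose 8 of 41 patients in one arm withdraw and the remaining 41 − 8 = 33 show no severe reaction. The one-sided 95% upper limit from 0 of 33 is 1 − 0.05^(1/33) = 0.087, or 8.7%. Let k of the 8 have had such a reaction; k is an assumption:

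| k | Proportion among the 41 |
|---|---|
| 0 | 0% |
| 2 | 2/41 = 4.9% |
| 3 | 3/41 = 7.3% |
| 4 | 4/41 = 9.8% |
| 8 | 8/41 = 19.5% |

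Each uncounted patient is worth 1/41 = 2.4 percentage points. The proportion passes the reported limit only from k = 4. A few uncounted events can therefore matter in arms of this size, but nothing in the article says that k would be that large.

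**The case against.** **The rules do not conflict.** An event can be recorded when it happens and its record deleted later, so the recording rule and the deletion option can both be followed. This stands. A reader might infer an outright contradiction, but the text shows only that the rules have not been fitted together.

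**The scope of deletion belongs in the consent form or full protocol.** This stands in part. An article need not define deletion in detail, and silence on its own would be no finding. But the article does state an unlimited deletion option, treatment after withdrawal and the exclusions, and those stated rules combine badly.

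**Nothing says that harm would be erased or later events missed.** This stands. A reader might infer that a harmed patient leaves no trace, or that events during continued therapy go unrecorded. The article says neither: deletion is optional, and 2.3.2 and 2.3.3 have clinicians monitor over the whole course of therapy without a cut-off at withdrawal. Nor does it say that withdrawal is a likely response to a reaction.

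**Severe reactions have their own route.** They are documented and lead to reassignment, with no mention of deletion. This protects the record but not the count, since reassigned patients are also excluded. Nor does the route clearly cover a patient who leaves on her own initiative after a milder or undisclosed reaction.

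**The exclusions are meant for efficacy.** The reasons given are crossover, comparability of the groups and validity of responses, which suggests questionnaire data. That is a fair reading, but the wording is general, and one sentence exempting adverse events would settle it.

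**Continued care after withdrawal is a protection.** Agreed; it is not criticised here.

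**Conclusion.** The point holds as a gap between stated rules. Two losses should be kept apart. The firmer one is that withdrawn and reassigned patients are excluded from analyses with no exception for adverse events; this applies whether or not anyone requests deletion, and it can be reversed while the records exist. The second is only possible: adverse-event records may be deleted because the option in 2.4.1 has no stated limit. It would be permanent.

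The size cannot be estimated from the article. A reader might take 24 patients, or 8 per arm, as the expected number of deleted records. They are ceilings that need every anticipated dropout to request deletion and, for the per-arm figure, all dropout to follow allocation evenly. The direction is also an assumption: the harm comparison is biased only if reactions lead to withdrawal or reassignment more often in one arm than in another. The rules are cheap to repair before consent is taken, and lost records cannot be repaired afterwards.

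**What to change.** 1. In 2.4.1 and the consent form, state that adverse-event records made up to withdrawal are kept in coded form and fall outside the deletion option. Other data can stay deletable; a wider restriction is not needed for this point.
2. In 2.4.2, ask patients who stop the questionnaires but remain in therapy for consent to continued adverse-event recording.
3. In 2.3.2, 2.3.3, 2.4.2 and 2.6, state that the exclusions do not apply to adverse events.
4. In 2.6, commit to reporting adverse events and withdrawals by randomised arm for everyone randomised. A comparison with TAU needs the same recording there; 2.3.1 has no sentence matching those in 2.3.2 and 2.3.3.
5. Reconcile 2.4.2 (remains on the assigned condition) with 2.3.2 and 2.3.3 (reassigned to TAU) for patients who withdraw because of a reaction. Which rule applies is a clinical decision for the investigators.

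**Cost.** Amended protocol and consent wording, submitted to the ethics committee, ideally before enrolment. No extra patients or visits are needed, though recording has to continue for consenting patients who stay in therapy. The real downside is a somewhat narrower deletion right, which must be disclosed at consent and depends on ethics committee approval.
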